## Abstract

**Background:**

One of the toughest decisions faced by elderly people is whether to stay at home or move to a care facility. This study seeks to evaluate the impact of training interprofessional home-care teams in shared decision making combined with a decision aid on the proportion of elderly people who report being active in the decision-making process regarding whether to stay at home or move to a care facility.

**Methods/Design:**

We propose a multicenter cluster randomized trial conducted with home-care interprofessional teams in the Province of Quebec with 2 data collection phases: before and after the intervention. Units of randomization will be centers for primary healthcare and social services. We will enroll 16 of these and ask each to provide one home-care interprofessional team involved in decisions and care planning with eligible clients. Clients will be included if they i) are aged ≥65; ii) are receiving care from the participating home-care interprofessional team; iii) have faced the decision about staying at home or moving to a care facility in the past 3 to 6 months; iv) are able to read, understand and write French or English; and v) are able to give informed consent. If clients are unable to provide informed consent, their primary caregiver who was involved in the decision-making process will be eligible to participate. The intervention arm will receive training in shared decision making and use of a decision aid. The control arm will receive ‘usual care’. The primary outcome of interest is the assumed role in the decision-making process as assessed in clients or caregivers with a modified version of the Control Preferences Scale. Multilevel modeling will be used to take the hierarchical structure of the data into account. The study has obtained full ethical approval. The trial will comply with CONSORT guidelines adapted for cluster randomized trials.

**Discussion:**

Home care is a rapidly growing sector and this study will lay the foundations of a national strategy to ensure that IP home-care teams provide the highest quality of care for seriously ill elderly people and support for their families.

**Trial registration:**

ClinicalTrials.gov NCT02244359 (registered 18 September 2014).

**Electronic supplementary material:**

The online version of this article (doi:10.1186/s13063-015-0567-7) contains supplementary material, which is available to authorized users.

## Background

Striving to provide the right care in the right place and at the right time for an aging population requiring care is a priority issue for most ministries of health across Canada [1,2]. One of the toughest decisions for elderly people in Canada is whether to remain at home (with or without assistance) or move to a residential care facility [3]. Because this decision is rarely clinically cut-and-dry and is highly preference-sensitive [4,5], it requires shared decision making (SDM) [6]. Shared decision making, a process whereby health professionals and clients work together to make healthcare choices, is fundamental to informed consent and client-centered care [7-10]. Given the emphasis on integrated healthcare services and engagement of clients as partners in their care, finding effective ways to involve clients in sharing decisions with healthcare teams is critical [11-13]. An interprofessional (IP) approach to SDM (IP-SDM approach) is especially relevant to home-care teams working with elderly people. IP-SDM enables IP teams to support them in facing decisions, meet their decisional needs, and reach healthcare choices that are agreed upon by the client, family members/caregivers and the IP team together [14-16]. Since 2007, our team has worked toward expanding SDM beyond the physician-client dyad to IP teams [17] while aiming for rigorous evaluation of interventions for implementing SDM in clinical practice [18]. A previous study found that, overall, home-care providers intend to engage in an IP-SDM approach with elderly people but that various barriers interfere with them doing so [19]. We therefore developed a training program in SDM [20] combined with a decision aid and piloted these with one IP home-care team in Quebec City and one in Edmonton. However, we did not evaluate its impact on clinical practices nor on clients and their caregivers. Therefore, in this study, we seek to evaluate the impact of training IP home-care teams in SDM combined with a decision aid on the proportion of elderly people who report being active in the decision-making process regarding whether to stay at home or move to a care facility.

## Methods/Design

### Trial design and setting

We propose a multicenter cluster randomized trial conducted with home-care IP teams in the Province of Quebec and with 2 data collection phases: before (pre) and after (post) the intervention (Figure 1). The unit of randomization will be the center for primary healthcare and social services (CPHSS). CPHSSs (known in Quebec as *Centres de santé et de services sociales*) are the result of mergers between local community service centers, long-term care facilities and, in most cases, a hospital. The CPHSS is accountable for providing the local population with accessibility, continuity and quality of care. Our proposed study design decreases the potential of contamination bias since our proposed intervention targets one home-care IP team in each eligible CPHSS. During 2 data collection phases (pre- and post-intervention), we will assess the outcomes detailed below. Clients and caregivers will not be the same for pre- and post-intervention data collections, but IP teams and providers will be the same. Ethics committee review approval has been obtained from the CHU de Québec multicenter ethics committee (approval number: MP-CHU-QC-14-001). This trial is registered at clinicaltrials.gov (registration number: NCT02244359).

**Figure 1 Fig1:**
[figure not shown]
**Study flow diagram.** CPHSS, center for primary healthcare and social services; IP, interprofessional; IP-SDM, interprofessional approach to shared decision making.

### Engagement with and inclusion of clients, their families and caregivers

The proposed project builds on a long history of successful partnerships with clients’ and caregivers’ representatives. The IP-SDM conceptual model [15,16,21], the decision to be addressed and the training in SDM combined with a decision aid [22] to be evaluated were all identified and developed with stakeholders. Moreover, we have involved 2 caregivers’ representatives (LR, HB), one of whom is a representative of a nonprofit organization who is dedicated to representing caregivers in the writing of this proposal. HB reviewed all questionnaires to ensure their acceptability by clients and caregivers.

This project builds on previous successful client/caregiver partnerships as well as on successful relationships with healthcare organizations such as the CPHSS. An advisory board including representatives of all stakeholders is providing guidance throughout the project.

### Inclusion/exclusion criteria for participants and recruitment

We will target all CPHSSs in the eastern part of the Province of Quebec [23]. We will contact the directors of all potentially eligible CPHSSs in a random manner. We will present the project and seek their interest in participating in the study. One home-care IP team who is involved in decisions and care planning with eligible clients in participating CPHSSs will be eligible to participate in the trial. An IP healthcare team refers to the presence of a minimum of 2 healthcare providers from different professions involved in client care and who collaborate to provide integrated and cohesive client care [24,25]. Clients will be included if they i) are aged ≥65 years; ii) are receiving care from the home-care team; iii) have faced the decision about whether to stay at home or move to a care facility in the previous 3 to 6 months; iv) are able to read, understand and write French or English; and v) are able to give informed consent. For clients who cannot provide informed consent, we will identify the primary caregiver who was involved in the decision of interest. Clients will be recruited by the research team in a consecutive manner. We will keep detailed information on the flow of clients throughout the trial. All participants (providers, clients and caregivers) will sign consent forms approved by the ethics boards of the 16 CPHSSs (see detailed list, Additional file 1).

### Intervention arm

This intervention will include training in SDM and a decision aid. More specifically, the training in SDM will include i) a 1.5-hour online tutorial, based on the Ottawa Decision Support Tutorial [26], and ii) a 3.5-hour skills building workshop, which includes a video that demonstrates SDM in the context of IP home-care teams. Providers will be asked to give clients and their caregivers a copy of the decision aid. The intervention will be staggered over a 6-month period.

### Control/usual care arm

The providers and clients from the control group will not receive any particular intervention apart from the completion of data collection forms. We call the control group ‘usual care’ because clients from the control group will be exposed to the standard procedure for decisions regarding location of care currently in use in the Province of Quebec. This procedure will also be used in the intervention group.

### Allocation of participants to trial groups

Potential confounding variables will be controlled by randomization. The unit of randomization will be the CPHSS with stratification by urban or rural setting [27]. For CPHSS enrollment, 2 random lists will be prepared to establish the order in which CPHSSs will be contacted. We will follow this order systematically until the enrollment of 4 urban and 12 rural CPHSSs is complete.

A second randomization will occur after participants have completed their baseline measures. This randomization will be stratified to minimize the differences within groups due to geographic location. Thus, 2 urban and 6 rural CPHSSs will be allocated to each group. Randomization and allocation will be done using computer software, and data will be entered by an experienced, independent biostatistician.

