### Proposed frequency and duration of follow-up

There will be 2 data collection phases: 1) the pre-intervention data collection, lasting 3 months (for a sample of 5 clients/CPHSS), will be used to compare CPHSSs (intervention versus control) on the basis of the CPHSS clientele profile on the proportion of clients reporting an active role in the decision-making process about whether to remain at home or move to a care facility; and 2) postintervention, lasting 10 to 12 months.

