### Statistical consideration

#### Sample size

The primary outcome of interest is the proportion of elderly people who report an active role in the decision-making process regarding whether to stay at home or move to a care facility. Our estimate of the sample size is based on our updated reviews of interventions to improve the uptake of SDM [43] and earlier studies in primary care, in which we observed a 20% absolute difference between groups with an expected baseline value of 50% for the active role [44]. Our biostatisticians provided a number of scenarios with ICCs ranging from 0.02 to 0.05 and the number of clusters ranging from 12 to 16. We used a conservative value of ICC of 0.05 as the upper limit. In order to detect a difference of 20% (50% to 70%) between the intervention group and the control group after the intervention with 80% power, and a 5% significance level, we would require a total of 186 clients for an individually randomized trial. In considering an ICC of 0.05 and 16 clusters (CPHSSs), we would need a sample size of 456 clients in total. Allowing for a 10% loss to follow-up, 501 clients will be recruited (32/CPHSS). We will also recruit 5 clients/CPHSS before the intervention. This is deemed a sufficient number to be able to compare CPHSSs (experimental versus control) at trial entry on the basis of their clientele profiles [45].

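### Baseline data are in hand at all 16 CPHSSs before allocation, yet balance rests on urban/rural alone and covariate adjustment waits on observed imbalance; naming the model in advance would bring a modest gain

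*Protocol article*

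**What the plan says.** The section on allocation of participants to trial groups opens with the statement "Potential confounding variables will be controlled by randomization". It continues: "The unit of randomization will be the CPHSS with stratification by urban or rural setting". Allocation comes after the pre-intervention phase ("A second randomization will occur after participants have completed their baseline measures"), and "2 urban and 6 rural CPHSSs will be allocated to each group". No other balancing factor is given.

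The pre-intervention sample is small: "We will also recruit 5 clients/CPHSS before the intervention" (Sample size). According to the section on frequency and duration of follow-up, these data "will be used to compare CPHSSs (intervention versus control) on the basis of the CPHSS clientele profile on the proportion of clients reporting an active" (the last word refers to the client's part in the decision). The analysis plan gives them one further use, as performance feedback in the workshop. The clients differ between phases but the teams do not: "Clients and caregivers will not be the same for pre- and post-intervention data collections, but IP teams and providers will be the same" (Trial design and setting).

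The analysis plan compares organizational and socio-demographic characteristics between the arms and enters potential confounders as covariates should any emerge. The primary outcome goes into a multilevel logistic model (GLIMMIX). Neither the urban/rural stratum nor the pre-phase active-role answers are named as terms in it.

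**The concern.** With 8 clusters per arm, randomization removes systematic bias but does not secure balance in the one allocation that is drawn. A trial that holds data on all its clusters before it allocates can use them in two ways: by restricting the allocation, and by fixing in advance a model that contains them. The article commits to neither.

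The rule it does state is to look for differences between the arms and then adjust for what is found. The primary model thus depends on the observed data. For the active-role proportion, that decision would rest on 5 clients per centre, so it would respond largely to sampling noise. At stake are some precision and the clarity of the primary analysis.

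**Working it through.** **Inputs from the article.** 16 CPHSSs (4 urban, 12 rural; 8 per arm); 5 pre-phase clients per CPHSS (80 in all, 40 per arm); 50% versus 70%; 5% significance; 80% power; ICC 0.05 as the upper limit of a 0.02 to 0.05 range; 456 clients, i.e. 456/16 = 28.5 per CPHSS.

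**Assumptions, not in the article.** A two-sided test; a correlation c of true centre rates between phases of 0.5 to 1; and, for the balance calculation, four independent CPHSS-level measures.

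**1. The plan's own figures.** Per arm, [1.96·√(2·0.6·0.4) + 0.842·√(0.25 + 0.21)]² / 0.2² = 93, so 186 in total, as stated. With 30 clients per cluster (assumed), the design effect is 1 + 29·0.05 = 2.45, and 186·2.45 = 455.7, which gives the stated 456.

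**2. Chance imbalance in the true baseline rate.** At ICC 0.05 and 50% active:
- the between-centre SD is √(0.05·0.25) = 0.112;
- the true 8 v 8 gap has SD 0.112·√(2/8) = 5.6 points (95% range about ±11), against a target effect of 20 points;
- at ICC 0.02 the SD is 3.5 points (about ±7).

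These figures take no credit for the urban/rural stratification.

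**3. What 5 clients per centre reveal.** The observed 40 v 40 gap has SD √(2·0.25·1.2/40) = 12.2 points, most of it sampling error. The reliability of a centre's pre-phase proportion is R0 = 5·0.05/(1 + 4·0.05) = 0.208.

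**4. Precision gain from using the pre-phase answers.** For the post-phase mean, R1 = 28.5·0.05/(1 + 27.5·0.05) = 1.425/2.375 = 0.600. The share of variance removed is R0·R1·c² = 0.125·c². The unadjusted standard error is √(0.46·2.375/228) = 0.0692, so effect/SE = 0.20/0.0692 = 2.89. Power uses the t distribution with 14 df unadjusted and 13 df adjusted.

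| ICC | c | Variance removed | Power before | Power after |
|---|---|---|---|---|
| 0.05 | 0.5 | 3.1% | 76.6% | 77.4% |
| 0.05 | 0.8 | 8.0% | 76.6% | 79.5% |
| 0.05 | 1 | 12.5% | 76.6% | 81.4% |
| 0.02 | 0.5 | 0.9% | 91.3% | 91.2% |
| 0.02 | 1 | 3.4% | 91.3% | 91.9% |

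The way the data enter the model matters. In simulation at ICC 0.05, post-phase data alone gave about 76% power. Adjusting simply for the noisy centre mean gave 73.6%, 75.6% and 77.6% at c = 0.5, 0.8 and 1. A structured joint model of both phases gave 77.1%, 79.2% and 80.9%.

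**5. Room for restricted allocation.** There are C(4,2)·C(12,6) = 6·924 = 5,544 stratified allocations. All were scored on four measures, one of them the pre-phase proportion. Over all allocations the arm gap in a measure has SD 0.50 SD units, and 80% of allocations have at least one gap above 0.5. Among the best-balanced tenth (about 554) these become 0.22 and about 1.5%.

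**6. What that does for the true active-role gap.** Reducing the observed imbalance from 0.50 to 0.22 SD leaves a true-gap SD of 5.6·√(1 − 0.208·(1 − (0.22/0.50)²)) = 5.1 points. Simulation agrees (about 5.5 to 5.1). Even perfect balance on the observed proportions would leave 5.6·√(1 − 0.208) = 5.0 points.

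**The case against.** The case for leaving the plan alone is substantial. Stratified randomization of 2 + 2 urban and 6 + 6 rural centres is valid and consistently described, and restricted allocation is an alternative rather than a correction. The 0.50 SD and 80% figures hold for any 8 v 8 split with four independent measures. The article does not say how strongly any such measure predicts the outcome, and imbalance in a non-prognostic measure does no harm. The precision gain rests on a correlation that the article does not give and nearly vanishes at ICC 0.02. All of this stands and limits the point to an inexpensive refinement.

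It can also be said that covariate lists belong in a statistical analysis plan, which is not shown. That would answer a complaint about missing detail. Here, however, the article states a rule, and the rule makes adjustment depend on what the comparison of arms shows.

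Three stronger readings are tempting but unsupported:
- **That the primary model ignores the baseline data.** It does not exclude them: the arms are to be compared on the pre-phase active-role proportion, and potential confounders may enter as covariates. They are simply not named in advance.
- **That restriction would remove most of the imbalance in the outcome.** In the enumeration, the chance of an observed pre-phase gap strictly above 10 points falls from about 35% to 2%. That gap is mainly noise from 5 clients per centre; the true gap hardly moves (5.6 to 5.1 points).
- **That the design is biased.** Randomization protects against that whatever imbalance chance produces.

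**Conclusion.** The point holds as a minor improvement. The article has baseline data on every cluster before it allocates, balances on one factor, and leaves the primary model's covariates to be settled by observed imbalance. The consequence is a data-dependent covariate choice and a small loss of precision: about 3 to 12% of the variance and 1 to 5 points of power at ICC 0.05, and less than 1 point at ICC 0.02. These sizes assume a pre/post cluster correlation of 0.5 to 1, 28.5 analysed clients per CPHSS, and variance components known well enough for the joint model to reach its theoretical gain. The stronger argument is for fixing the model in advance; the benefit of restricted allocation depends on how prognostic the chosen measures are, which the article does not say.

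**What to change.** **Analysis plan.** Keep the post-intervention difference between arms as the estimand. Replace the conditional covariate rule with a primary model named in advance that:
- includes the urban/rural stratum;
- fits pre- and post-phase answers together, with a common baseline across arms (justified because the pre-phase precedes allocation);
- has a CPHSS random effect shared by both phases and a CPHSS-by-phase term.

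Do not substitute a simple adjustment for the 5-client centre proportion, which gave no reliable gain. State a fallback in case the CPHSS-by-phase variance cannot be estimated from 80 pre-phase answers in 16 centres.

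**Allocation (optional, and only if it has not yet been made).** Have the independent biostatistician draw at random from the best-balanced tenth of the 5,544 stratified allocations, scored on a few CPHSS or clientele measures already collected. Name those measures beforehand and carry them into the model. Soften the sentence on control of confounding: randomization prevents systematic differences between arms but does not ensure balance with 8 clusters in each.

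**Cost.** A short program and a few sentences of protocol or SAP text, with no extra clients or data. The price is a somewhat more complex model.

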### Protecting against sources of bias

Given the nature of this trial, the investigators, research assistants (who will enroll participants) and participating CPHSSs and their IP home-care teams will not be blinded to group allocation because they will be aware of which CPHSSs are receiving the intervention. However, sources of bias will be minimized by the following procedures:Strict allocation concealment will be respected by using standardized tools and by instructing research assistants not to tell clients to which group their IP home-care team has been randomized. Moreover, each research assistant will collect data only on the intervention group or only on the control group; they will not change trial arms.The design of data collection forms and packages will be similar in both groups.Double data entry will be centrally performed by 2 independent data clerks who will attribute a secret group code to intervention and control groups and will thus be blinded to group allocation.Data analyses will be performed blindly by our study biostatistician who will not be involved with randomization.Team members will access the group code only after analyses and interpretation of the results are completed. Recruitment of clients will be sequential and will be performed by a research assistant who will be given names of potentially eligible clients directly from a central registry that is in place in all CPHSSs. She/he will then approach all potentially eligible participants consecutively, thus reducing selection bias. We do not expect that providers in the participating CPHSSs will influence one another regarding the intervention, particularly given the significant geographical distance between IP home-care clinical sites. Sociodemographic data in each group will be compared to assess confounding variables.

### Proposed frequency and duration of follow-up

There will be 2 data collection phases: 1) the pre-intervention data collection, lasting 3 months (for a sample of 5 clients/CPHSS), will be used to compare CPHSSs (intervention versus control) on the basis of the CPHSS clientele profile on the proportion of clients reporting an active role in the decision-making process about whether to remain at home or move to a care facility; and 2) postintervention, lasting 10 to 12 months.

### Outcome measures

The primary outcome of interest is the assumed role in the decision making. We will use the modified version of the Control Preferences Scale [28] designed to assess the assumed role in the decision-making process reported by the client or the caregiver [29]. The scale consists of a single question to assess the client’s perception of locus of control over the decision-making process. This is the scale used most in studies assessing the implementation of SDM in clinical practices [18,30]. It is responsive to change and correlates with patients’ as well as with clinicians’ reported levels of patient involvement [31]. Response options (n = 5) are as follows: A) I made the decision; B) I made the decision after seriously considering my providers’ opinions; C) My providers and I shared the responsibility for the decision making; D) My providers made the decision after seriously considering my opinion; E) My providers made the decision. A and B represent a client-controlled decision-making process, C represents a shared decision-making process, and D and E represent a practitioner-controlled decision-making process [29]. We will combine A, B and C to identify the proportion of clients reporting an active role in the decision-making process, and we will combine D and E to identify a passive role. We will perform our analysis by assessing the increase in the percentage of clients reporting an active role.

Measures of secondary outcomes will be collected. More specifically, in clients and caregivers, we will assess their preferred and chosen option (remain at home or move to care facility); decisional conflict using the Decisional Conflict Scale [32,33]; decisional regret using the Decisional Regret Scale [34]; HR-QoL (only in client) using 2 subscales from the Nottingham Health Profile: Social Isolation and Emotional Reactions [35-38]; and burden of care (only in caregivers) using a validated scale [39-42].

In providers, at study entry and exit, we will assess their intention to engage in SDM behaviors in the context of an IP home-care team sharing the decision with elderly people about whether to stay at home or move to another location.

